# ONE SHOT - single shot radiotherapy for localized prostate cancer: study protocol of a single arm, multicenter phase I/II trial

**DOI:** 10.1186/s13014-018-1112-0

**Published:** 2018-09-04

**Keywords:** Prostate cancer, Stereotactic body radiotherapy, Urethra-sparing, Single fraction, Quality of life, Electromagnetic transponders

## Abstract

**Background:**

Stereotactic body radiotherapy (SBRT) is an emerging treatment alternative for patients with localized prostate cancer. Promising results in terms of disease control and toxicity have been reported with 4 to 5 SBRT fractions. However, question of how far can the number of fractions with SBRT be reduced is a challenging research matter. As already explored by some authors in the context of brachytherapy, monotherapy appears to be feasible with an acceptable toxicity profile and a promising outcome. The aim of this multicenter phase I/II prospective trialis to demonstrate early evidence of safety and efficacy of a single-fraction SBRT approach for the treatment of localized disease.

**Methods:**

Patients with low- and intermediate-risk localized prostate cancer without significant tumor in the transitional zone will be treated with a single SBRT fraction of 19 Gy to the whole prostate gland with urethra-sparing (17 Gy). Intrafractional motion will be monitored with intraprostatic electromagnetic transponders. The primary endpoint of the phase I part of the study will be safety as assessed by CTCAE 4.03 grading scale, while biochemical relapse-free survival will be the endpoint for the phase II. The secondary endpoints include acute and late toxicity, quality of life, progression-free survival, and prostate-cancer specific survival.

**Discussion:**

This is the first multicenter phase I/II trial assessing the efficacy and safety of a single-dose SBRT treatment for patients with localized prostate cancer. If positive, results of ONE SHOT may help to design subsequent phase III trials exploring the role of SBRT monotherapy in the exclusive radiotherapy treatment of localized disease.

**Trial registration:**

Clinicaltrials.gov identifier: NCT03294889; Registered 27 September 2017.

## Background

Total dose and dose per fraction play an important role in the curative treatment of prostate cancer with radiotherapy (RT). Modern image-guided external RT allows safe dose escalation for prostate cancer. Doses above 74 Gy with conventional fractionation (2 Gy/day) have been shown to be beneficial. There are strong radiobiological considerations that suggest that treatment with a small number of large fractions (hypofractionation) may increase the therapeutic ratio of RT for prostate cancer.

The “α/β” ratio (i.e., cell sensitivity/cell repair) is a key parameter of the cell-survival linear-quadratic (LQ) model that purportedly defines the sensitivity of each tissue (healthy or tumoral) to changes in treatment fractionation. Prostate cancer cells may have a low α/β ratio (i.e.,~ 1.5 Gy), lower than that of most tumors or even of the late-responding normal tissues surrounding the tumor, the rectum and the bladder (α/β ratio 3–5 Gy) [1]. Thus, hypofractionation may increase the tumor cell killing effect with relatively less toxic effect on the surrounding late responding normal tissues compared to conventional fractionation. Several authors have reported their respective experiences with moderate hypofractionation (i.e., dose per fraction 2.5 Gy to 4 Gy) for prostate cancer confirming the equivalence in terms of disease control and tolerance compared to standard fractionated treatments [2–5].

Bio-mathematical models using large patient data sets have focused on external beam RT schedules using less than 4 Gy fractions. It deserves to be acknowledged that the LQ model may not be predictive of cell survival and isoeffects with doses per fraction above 3-4Gy. Indeed, the predictions of the LQ model at very high dose/fraction (extreme hypofractionation) may be somehow “ambivalent”, either overestimated (less repair of sublethal damage thus a lower value for “β”) or underestimated (increased indirect cell-death secondary to intravascular endothelial damage). Staring from this background, clinical research on extreme hypofractionation started some 15 years ago when stereotactic body RT (SBRT) technology appeared as a treatment option against localized prostate cancer competing with high-dose rate brachytherapy (HDR-BT).

Indeed, preliminary results on extreme hypofractionation with SBRT have been reported during the last few years mainly for low-risk patients in single-institution [6–8] or multi-institutional [9] series. Most frequently, 5 fractions of 7.25 Gy have been delivered for a total equivalent dose to the tumor of 90 Gy in 2 Gy/fraction (LQ model) and a success rate of > 90%, 5-year biochemical relapse-free (bRFS) survival rates [10]. Data published so far for prostate SBRT have shown, although with a limited follow-up, late grade 3 toxicity rates for rectal and genitourinary (GU) toxicity lying within a ≤ 3% range [8, 11, 12]. Although, caution is recommended to avoid passing a too optimistic message regarding the potential biological benefits of extreme hypofractionation for prostate cancer (i.e., more cure with less side effects), financial and logistical advantages can undoubtedly be foreseen. In fact, a drop from 40 or more treatments to 5 or less sessions may reduce the cost of external beam RT, will increase the availability of treatment slots in otherwise busy departments (important issue in countries with limited resources), and significantly improve patient’s convenience.

The question of how far can the number of fractions with SBRT be reduced is an exciting research matter with an undoubtful goal, face the challenge of assessing the potential for cure of prostate cancer patients with a single and unique fraction of high dose irradiation similar to what is already undertaken with radiosurgery against brain, lung, and liver targets. Such type of effort has already been attempted with HDR-BT. Recently, Prada et al. [13] reported a relatively disappointing 66% 6-year bRFS survival though a very good tolerance after a single interstitial application of 19 Gy to the prostate. Reasons for this suboptimal result may be related, for instance, to a suboptimal dose-distribution with HDR-BT compared to SBRT. Hoskin et al. have recently published the results on 49 patients treated with a single fraction of HDR-BT to 19/20 Gy [14]. With 49 months median follow-up, the 4-year estimates of grade-3 GU and gastrointestinal (GI) toxicity was 2% and 0%, respectively, with no grade 4 events, while the 4-year bRFS was 94%. Similarly, Morton et al. confirmed with a median follow-up time of 20 months the good tolerance of a single 19 Gy single HDR-BT fraction in terms of toxicity and impact on quality of life (QoL) [15] and Krauss et al. reported a 3-year bRFS rate of 93% [16], similar to results observed by Hoskin et al. In conclusion, for the authors one single fraction HDR-BT is feasible, weakly toxic, and with promising preliminary results.

Although, the effects are mostly encouraging, only controlled studies are able to properly address the impact of single fraction SBRT in prostate cancer outcomes. Therefore, a phase I/II approach will be a properly controlled study to demonstrate early evidence of safety and efficacy of the intervention and substantiate further the role of a single-fraction SBRT approach. If positive, the results of ONE SHOT will help determine the design of subsequent phase III trials in the exclusive RT setting for the treatment of localized disease.

## Methods/Design

This study was approved by the Ethics committee of the Geneva University Hospital (2017–01236) and is registered on clinicaltrials.gov (NCT03294889). This is a phase I/II, prospective, multicenter, single-arm study.

### Phase I, safety evaluation

The main objective of the phase I trial is to determine if a single fraction SBRT, with a dose of 19 Gy, is safe and well tolerated by assessing the occurrence of Grade ≥ 3 acute adverse events (AE) during the first 3 months.

### Phase II, efficacy evaluation

The main objective of the phase II trial is to determine if a single fraction SBRT, with a dose of 19 Gy, is an effective treatment option by assessing bRFS at 3 years.

#### Objectives

##### Primary endpoint of the phase I trial

Grade ≥ 3GU and GI acute AE will be assessed during the first three months following the single fraction treatment. AEs will be assessed according to National Cancer Institute Common Terminology Criteria for Adverse Events (NCI CTCAE) v4.03. Special attention will be given to diarrhea, fecal incontinence, proctitis, rectal hemorrhage, rectal pain, hematuria, urinary frequency, urinary urgency, urinary retention, urinary incontinence, and cystitis non-infective. Persistent AE will be defined as any persistent toxicity during the first 3 months post-treatment (follow-up milestones: 1 week, 6 weeks, and 12 weeks).

##### Primary endpoint of the phase II trial

bRFS, from time of inclusion until biochemical progression (according to recommendations of the Radiation Therapy Oncology Group - American Society for Radiation Oncology (RTOG-ASTRO), the Phoenix Consensus Conference recommendations) [17]:A rise by 2 ng/ml or more above the nadir prostate specific antigen (PSA) confirmed by a second observation taken 3–4 weeks later, where the nadir PSA is defined as the lowest PSA value observed on study.

##### Secondary endpoints of the phase II trial

Acute AE (during the first 3 months follow-up) according to CTCAE v4.03Late AE (after 3 months follow-up) according to CTCAE v4.03Progression free survival (PFS) defined as time from inclusion until one of the following events, whichever comes first:Biochemical progressionClinical progression defined as either local or regional recurrence of the disease or the appearance of distant metastasesDeath from any causeStart of another line of systemic anti-neoplastic therapyClinical progression free-survivalLocal progression free-survivalTime to further anti-cancer therapy defined as the time from inclusion to the start of any type of salvage treatment.Prostate cancer-specific survival (PCSS)Overall survival (OS)QoL evaluated using EPIC 26 (Expanded prostate cancer index composite) [18], IPSS (International Prostate Symptoms Score) [19], and IIEF-5 (International Index of Erectile Function) [20]

#### Inclusion criteria

Written informed consent according to ICH/GCP regulations before registration and prior to any trial specific proceduresHistologically confirmed adenocarcinoma of the prostate without small cell featuresTumor clinical stage cT1c-2c, pN0 or cN0, M0, according to UICC TNM 2009Magnetic Resonance Imaging (MRI) staging must confirm American Joint Committee on Cancer (AJCC) stage T1, T2a, T2b, or T2cGleason score at biopsy 3 + 3 or 3 + 4 (World Health Organization, WHO 2016 Grade Groups 1, 2)PSA ≤15 ng/mlAge 18–85 years at time of registrationWHO performance status 0–1IPSS ≤10 (alpha blockers allowed)MRI-based volume estimation of prostate gland ≤70 ccPatient agrees not to father a child during trial treatment and during 6 months thereafter

#### Exclusion criteria

Evidence of T3a, T3b, or T4 disease as assessed by MRIPositive lymph-nodes or metastatic disease from prostate cancer on imaging studies.Significant tumor on the transitional zone as assessed by MRIPrevious or ongoing androgen deprivation therapyImpossibility to implant electromagnetic transponders into the prostateHistory of hematologic or primary solid tumor malignancy, unless in remission for at least 3 years from registration with the exception of curatively treated localized non-melanoma skin cancerPrior pelvic RTPrevious surgery for prostate cancerPrevious transurethral resection of the prostate (< 12 weeks before registration)Hip prosthesisSevere or active co-morbidity likely to impact on the advisability of SBRTAny other serious underlying medical, psychiatric, psychological, familial, or geographical condition, which in the judgment of the investigator may interfere with the planned staging, treatment and follow-up, affect patient compliance, or place the patient at high risk from treatment-related complications

#### Intervention

In this trial, patients with localized prostate cancer are registered to receive the following target SBRT dose:19 Gy in a single fraction to the whole prostate gland ± proximal seminal vesicles17 Gy in a single fraction to the urethra planning-risk volume (PRV)

Before the SBRT treatment, all patients will be implanted transrectally or transperineally under ultrasound guidance with three electromagnetic transponders, the *Calypso*® beacons (*Varian Medical Systems, Palo Alto, CA*). Patients will be simulated a minimum of 4 days after the implant and treated with an empty rectum and full bladder. To help with the contouring of the urethra a 12 *French Foley* non-radiopaque catheter will be inserted before the CT simulation and before irradiation. Rigid or deformable co-registration with multi-parametric MRI is to be used for contouring purposes.

The Clinical Tumor Volume (CTV) is defined as the prostate +/− the proximal 2/3 of the seminal vesicles (SV) based on the risk of SV involvement as determined by the *Roach* score using a cutoff threshold of 15% [21]. The planning target volume (PTV) is defined as the CTV plus 5 mm margins in all directions except for a 3 mm margin posteriorly towards the rectal wall. The urethra PRV is defined on CT images by contouring a 12 *French Foley* catheter with a 2 mm isotropic rim expansion. Organs at risk (OAR) are contoured according to RTOG guidelines [22] and include the bladder wall and the rectal wall (both defined as a 5-mm internal margin created from the external surface), the penile bulb [23], and the proximal femurs. All patients will be treated with megavoltage beams from a *TrueBeam®* linear accelerator (*Varian Medical Systems, Palo Alto, CA*) with nominal photon energies ≥6 MV, 6 degrees of freedom couch, and a *Calypso*® localization system. The irradiation technique is *RapidArc*® (*Varian Medical Systems, Palo Alto, CA*), a rotational technique using a flattening filter-free (FFF) modality with patients treated in an isocentric setting.

##### Dose prescription, recording and reporting

As volumetric modulated arc therapy (VMAT) techniques are mandatory in this trial, the definition of volumes and the dose reporting shall be in accordance with the ICRU (*International Commission on Radiation Units and Measurements*) report 83. The dose variation in the PTV shall be assessed by the near-minimum dose (D98%) and near-maximum dose (D2%). The proposed treatment verification schedule is presented in Fig. 1 using a threshold limit for *Calypso*® of ±3 mm with geometric check limits set to 2 mm (geometrical residual) and rotations of 10° (default values). Table 1 summarizes the dose constraints for the OAR [24].

**Fig. 1 Fig1:**
[figure not shown]
Image-guided flowchart as per protocol

**Table 1 Tab1:** Dose constraints

Structure	Standardized nomenclature	Dosimetric Parameter	Per Protocol	Acceptable Variation
PTV_19	PTV_19	D98% (Dnear min)	≥ 95% (i.e. 18 Gy)	
		D2% (Dnear max)	≤ 107% (ie. 20.3Gy)	D5% ≤ 107%, D2% ≤ 110%
Rectal_wall	Rectal_wall	V9.5Gy (50%)	< 40%	40–50%
		V15Gy (80%)	< 15%	15–20%
		V17Gy (90%) (NTD 68 Gy)	< 10%	< 15%
		V19Gy (100%) (NTD 83.6 Gy)	< 5%	< 10%
		V20Gy (105%) (NTD 92 Gy)	< 1 cc	
Bladder_wall	Bladder_wall	V9.5Gy (50%)	< 50%	50–60%
		V15Gy (80%)	< 20%	20–30%
		V17Gy (90%) (NTD 68 Gy)	< 15%	15–20%
		V19Gy (100%) (NTD 83.6 Gy)	< 10%	< 15%
		V20Gy (105%) (NTD 92 Gy)	< 1 cc	
Femurs (each)	Femur_Rt Femur_Lt	V14Gy (NTD 48 Gy)	< 5%	5–10%
Penile bulb	Penile_bulb	V14Gy (NTD 48 Gy)	< 5%	5–10%
Urethra PRV	Urethra_PRV	D98% (Dnear min)	≥ 95% (i.e. 16.2 Gy)	
		D5%	≤ 107% (i.e. 18.2 Gy)	
		D2% (Dnear max)	≤ 110% (i.e. 18.7 Gy)	

##### Radiation Therapy Quality Assurance (RTQA)

A RTQA program is based in Geneva and is an important asset of this multicentric trial. Electronic submission and assessment of target and OaR volumes, in addition to treatment plans as well, is a major step before any treatment can be validated and approved.

#### Follow-up

Patients are seen at day-5 after SBRT, at weeks 6 and 12, every 6 months for 2 years post treatment, and yearly up to 5 years of follow-up. A clinical update and a physical exam are conducted by recording any acute and/or late AE and the sequential PSA measurements. IPSS, IIEF-5, and QoL (EPIC-26 questionnaire) assessments are also performed. Radiological investigations including mpMRI, bone scan, choline-PET, and/or PSMA-PET will be repeated in case of progression, either biochemical or clinical.

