#### Phase II- statistical analysis of the primary endpoint

Efficacy analyses will be performed on an intention to treat basis (i.e., involving those patients following the major inclusion criteria and repeated one per protocol set). The primary endpoint is 3-years bRFS. bRFS, and its 97.5% one-sided confidence interval (CI), will be determined using the *Kaplan Meier* method. If the expected value of 96% isn’t included in this interval, the efficacy of the experimental treatment will be questioned.

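### 3-year bRFS is timed from inclusion but PSA visits are timed from SBRT, so on the nominal schedule most failures found at the 36-month visit fall after the 3-year reading

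*Protocol article*

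**What the plan says.** All places are in the protocol article.

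- **Clock.** Primary endpoint of the phase II trial: "bRFS, from time of inclusion until biochemical progression". Progression is a PSA rise of at least 2 ng/ml above nadir, "confirmed by a second observation taken 3–4 weeks later".
- **Reading point.** Phase II, efficacy evaluation: the aim is to judge whether the treatment "is an effective treatment option by assessing bRFS at 3 years". The analysis section for the primary endpoint repeats it, "The primary endpoint is 3-years bRFS", and names Kaplan-Meier as the estimator.
- **Visits.** Follow-up: "Patients are seen at day-5 after SBRT, at weeks 6 and 12", then "every 6 months for 2 years post treatment, and yearly up to 5 years of follow-up". These visits include "recording any acute and/or late AE and the sequential PSA measurements". The scheduled PSA times after the early visits are therefore months 6, 12, 18, 24, 36, 48 and 60 after SBRT.
- **Between inclusion and SBRT.** Intervention: "Before the SBRT treatment, all patients will be implanted transrectally or transperineally under ultrasound guidance", with at least 4 days from implant to simulation. The RTQA section adds central submission and assessment of volumes and plans before treatment is approved.

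**The concern.** Biochemical failure becomes visible only when PSA is measured. If the visit meant to show year-3 failures falls after the point at which the curve is read, those failures are missing from the primary estimate. The two origins differ by the lag from inclusion to SBRT, which is above zero given the steps listed. The gap in front of the 3-year visit is a full year, so a small offset on the calendar can remove up to a year of failures.

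The error runs in the treatment's favour and grows as the treatment performs worse. In a single-arm trial, the 3-year estimate and its comparison with the expected 96% are the only test of efficacy.

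**Working it through.** **1. The plan's own figure.** The sample size follows from a Wald precision formula: n = 1.96² × 0.96 × 0.04 / 0.06² = 40.98, or 41 evaluable. Allowing 10% dropout gives 40.98 × 1.1 = 45.1 or 40.98 / 0.9 = 45.5, against 45 stated. The figure reproduces, and nothing below changes it.

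**2. Where the visits fall on the bRFS clock.** Time from inclusion = scheduled month after SBRT + lag. The article does not give the lag; I assume 0.25, 1 and 2 months (about 1 to 8 weeks).

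| Lag (months) | 24-month visit | 36-month visit |
|---|---|---|
| 0.25 | 24.25 | 36.25 |
| 1 | 25 | 37 |
| 2 | 26 | 38 |

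The confirming PSA adds a further 0.7 to 0.9 month. For any positive lag, the last scheduled PSA before month 36 is the 24-month one.

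**3. Size with visits exactly on schedule.** With a constant hazard and progression dated at the detecting visit, the expected Kaplan-Meier value at month 36 is S₃^((24 + lag)/36), where S₃ is the true 3-year bRFS. I use three truths: the planned 96%; 90%, the bound in the sample size section; and 81%. The last is the constant-hazard equivalent of the 66% 6-year result after single 19 Gy brachytherapy quoted in the Background: 0.66^(3/6) = 0.812.

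| Truth | Lag 0.25 | Lag 1 | Lag 2 | Upward bias (points) |
|---|---|---|---|---|
| 96% | 97.3% | 97.2% | 97.1% | 1.1 to 1.3 |
| 90% | 93.2% | 92.9% | 92.7% | 2.7 to 3.2 |
| 81.2% | 86.9% | 86.6% | 86.1% | 4.8 to 5.7 |

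**4. Allowing for visit scatter.** Simulating visits that vary around their scheduled date (SD 1.5 to 4 weeks) lets some 36-month visits fall before month 36. The bias becomes about 1.0 to 1.3, 2.3 to 3.2 and 4.3 to 5.7 points.

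**5. Against the planned precision.** The width of 0.06 holds only at 96%. By the same formula with 41 patients, 1.96 × √(p(1 − p)/41), it is 6.0 points at 96%, 9.2 at 90% and 12.0 at 81%. At its upper end the bias is 1.3/6.0 = 22%, 3.2/9.2 = 35% and 5.7/12.0 = 48% of the width.

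**6. Reading after the 36-month visit.** With a 1-month lag, that visit sits at month 37, so the expected value is S₃^(37/36): 95.9%, 89.7% and 80.8%. What is left is one extra month of hazard.

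**The case against.** - **Unstated rules.** The size depends on how progression is dated, how wide the visit windows are and exactly where the curve is read. An article may leave these to the full protocol or SAP, and their absence is not the point here. The point rests on what is stated: clock, visit origin, reading time and estimator, which do not line up as written. The objection does stand against treating the figures as more than conditional.
- **Other PSA values.** The article does not say that PSA is drawn only at scheduled visits, and a rising value at month 24 could prompt an earlier test. Visits also drift: with a lag of 2 to 8 weeks and SD 4 weeks, about 13% of 36-month visits precede month 36. With a lag of only 1 to 3 weeks and the same scatter, about 31% do, and the bias falls to roughly 0.9, 2.2 and 4.1 points. It shrinks but does not vanish.
- **Stronger readings.** A reader might infer that every failure found at the 3-year visit is lost and that the result is simply a 2-year figure. The documents support only 'most', on the nominal schedule. Nor is the bias nearly as large as the planned interval: that sets the bias at 81% against a width valid only at 96%. Larger biases under a rising hazard can be calculated, but nothing in the article supports that hazard shape. I also give no figure for the effect on the efficacy rule, because the article does not make clear which limit of its one-sided interval is to be compared with 96%.
- **Time zero.** A reader might conclude that the clock must move to SBRT. It need not. Inclusion fits the intention-to-treat analysis and the PFS definition, and patients included but never treated would have no SBRT date.

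**Conclusion.** The point holds as a misalignment in the stated text. Followed as written on the nominal schedule, the 3-year Kaplan-Meier estimate mostly reflects failures found by the 24-month visit and is biased upward by about 1.0 to 1.3 points at a true 96%, 2.3 to 3.2 at 90% and 4.3 to 5.7 at 81%. This assumes a constant hazard, progression dated at the detecting visit, a lag of 1 to 8 weeks and visit scatter SD 1.5 to 4 weeks. It also takes inclusion to mean entry before transponder implantation, the natural reading, and takes the yearly visits to be counted from SBRT like those before them. Dating progression at the confirming PSA would make it worse; early visits or extra PSA tests would make it smaller. At the planning value the effect is modest. It matters most if the treatment does poorly.

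**What to change.** - Date progression at the first qualifying PSA, once confirmed.
- Define 3-year bRFS as the Kaplan-Meier estimate read after the 36-month post-SBRT visit window and the 3-4 week confirmation have closed. An example is 39 months after SBRT: 36, plus about 1 for confirmation, plus about 2 for late visits. If the inclusion clock is kept for the intention-to-treat set, about 41 months after inclusion allows for a lag of up to 8 weeks. Moving the origin to SBRT without a later reading is not enough, because late visits would still miss the cut.
- Keep patients who are event-free at their 36-month visit in the risk set up to the reading point, for instance by using scheduled visit months for events and censoring alike. If they were censored on their own visit date, failures found at later visits would be divided by a shrinking risk set and the estimate would fall too far.
- As a sensitivity analysis, give an interval-censored (Turnbull) estimate with a confidence interval suited to that method.
- Treat the other yearly rates that depend on PSA visits in the same way.

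The cost is wording only: no added visits, PSA tests or patients, and 45 stands. The primary readout comes a few months later and may be slightly less favourable.
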